#### Statistical analysis method

The number of included and completed cases in the overall and each site is listed in the case analysis, and three analysis datasets (FAS, PPS, and SS) are generated. Dropouts and excluded cases along with the reasons for their dropping out and exclusion are listed.Demographic and baseline data analysis: Descriptive statistics of demographic data and other baseline characteristic values: For continuous variables, total number of cases, mean, standard deviation, median, and minimum and maximum values are calculated. The t-test will be used for normally-distributed data and the rank-sum test will be used for data with skewed distribution. Frequency and proportion are calculated for countable and grade data. The chi-square test will be used for disordered classification data, and the rank-sum test will be used for ordinal data. Inferential statistical results (*P*-values) are presented based on descriptive statistics.Efficacy analysis:A.Analysis of the primary efficacy indicators (overall response rate): The overall response rate is compared using the chi-square test, corrected chi-square test, or exact probability test. The 95% confidence interval of the difference in response rates between the two groups will be calculated, and if the lower limit of the confidence interval is greater than −10%, the result will be considered non-inferior.B.Analysis of the secondary efficacy indicators: Differences in the scores of NRS at each time point and the total score between the two groups are compared by the *t*-test or rank-sum test; differences in the physician satisfaction VAS score and the nurse satisfaction VAS score between the groups are compared by the t-test or rank-sum test; the difference between the two groups regarding willingness to undergo ablation surgery another time will be compared by the chi-square test, corrected chi-square test, or exact probability test; differences between the two groups with respect to duration of surgery, postoperative hospital stay, and average daily dose will be compared by the t-test or rank-sum test; the difference in the uninterrupted completion rate of surgery without complaints of pain between the groups will be compared by the chi-square test, corrected chi-square test, or exact probability test.Safety analysis: The incidence of adverse reactions will be calculated, their frequency and proportion were systematically listed, and the percentage calculated. A detailed list of cases of various adverse events (AEs), the number and rate of cases, conversion of physical examination indicators, ECG, respiratory and circulatory indicators, and laboratory indicators that “turn normal to abnormal” or “intensify abnormal” after the test, and list clinical explanations will be recorded.

### Confidentiality {27}

The medical records and information of participants will be kept completely at the hospital. Researchers, ethics committees, drug regulatory authorities, and health commission regulatory authorities will be allowed access to participants’ medical records. Any public reporting of the results of this study will not disclose the individual identity of the participants. In accordance with the principles of medical research ethics, except for personal privacy information, the trial data will be available for public inquiry and sharing, which will be limited to web-based electronic databases to ensure that no personal privacy information will be disclosed.

Researchers must ensure that the privacy of clinical trial subjects is maintained. In all documents submitted to the sponsor, only the subject number of the clinical trial shall be used to identify the participants of the trial, and the name and hospitalization number of the subjects shall not be specified. The investigator must maintain the name and address of the clinical trial subject and the enrollment form corresponding to the clinical study patient number. These entry forms are kept strictly confidential by the investigator and cannot be submitted to the sponsor. An electronic data capture system was used for data collection in this study. According to the GCP requirements of China, the clinical trial data shall be kept for 5 years after the termination of the clinical trial.

### Plans for collection, laboratory evaluation, and storage of biological specimens for genetic or molecular analysis in this trial/future use {33}

Not applicable. No biological specimens for genetic or molecular analysis are collected, evaluated, or stored in this trial.

## Statistical methods

### Statistical methods for primary and secondary outcomes {20a}

All subjects who were randomized, received the trial drug, and had data on at least one post-dose efficacy evaluation were included in the outcome analysis. The number of different organ tumors, single or multiple tumor tissues, and different ablation techniques were compared between the two groups to determine whether they were comparable.

Statistical analyses are performed using the SAS 9.4 software. Unless otherwise specified, the level of statistical significance was set at *P* ≤ 0.05. For a non-inferiority test, a one-sided test will be used, and *P* ≤ 0.025 are considered statistically significant.

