With the popularization of interventional therapy for cancer, pain caused by the therapy has become the major problem that medical staff and patients need to consider. The degree and duration of pain vary according to interventional radiology technique; additionally, there are great individual differences, such as radiofrequency ablation being accompanied by burning and tingling sensations in the viscera and skin [16]. A study on ablation therapy in patients with hepatocellular carcinoma [17] indicated that 70.6% and 25% of patients had an intraoperative pain score > 4 and > 8 points, respectively, with a higher pain level in patients with multiple ablations than in those with one ablation (6.76 ± 1.96 versus 5.28 ± 2.48). The sedation/analgesia guidelines for interventional diagnosis and treatment published by the European Society of Anesthesiology [18], the American Society of Anesthesiologists [19], the American Association of Interventional Pain Physicians [20], and the European Society of Cardiovascular and Interventional Radiology [21] recommend opioids such as morphine for analgesia before, during and/or after interventional surgery, to ensure good patient experience.

Opioids are the drugs of choice for the clinical treatment of pain, and morphine, being a classic opioid analgesic, is widely used in clinical practice [15, 22, 23]. Morphine is an opioid receptor agonist, has low lipid solubility and strong analgesic efficacy, and is mainly bio-transformed in the liver with a half-life of 2–4 h [24]. Although morphine has a positive analgesic effect, many patients cannot tolerate it and switch to other opioids due to adverse effects such as respiratory and circulatory depression [25–27], nausea and vomiting [28], and addiction [29].

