### Trial design {8}

This study is a superiority trial. We designed it by a multicenter, single-blind, randomized, parallel, positive-controlled clinical study to observe the efficacy and safety of nalbuphine hydrochloride injection and morphine hydrochloride injection for perioperative analgesia in tumor ablation. With such a study design, we hope to find a more effective and safe method of analgesia in the perioperative period for tumor ablation.

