#### Secondary outcomes

Pain intensity: Pain intensity was assessed by NRS at 1 min and 5 min after the start of ablation, at the end of surgery, and at 2 h, 6 h, 12 h, 24 h, and 48 h after surgery (at rest, during coughing, or during activity). Analgesic satisfaction: Evaluation of the degree of analgesic satisfaction. (A) Before leaving the operating room to assess the patient’s satisfaction with the analgesic effect; (B) before leaving the operating room, the surgeon and surgical nurse implement the satisfaction assessment; the satisfaction score uses the VAS, with a vernier ruler of 10 cm in length, marked with 10 scales, 0 point and 10 points at both ends, respectively, so that the patient, surgeon, and surgical nurse can mark the corresponding position that can represent their comfort on the ruler, and the follower can score it according to the position marked by the patient. A score of 0 represents extreme dissatisfaction and a score of 10 represents extreme satisfaction. Quality of life: One week after surgery, quality of life was assessed by telephone (using EORTC Quality of Life Inventory QLQ-C30 (V3.0).

We also collected patient demographics, history, physical and laboratory examinations, and surgical information, including tumor type, number of tumors ablated, size and location of lesions, and ablation technique.

All of these informations were recorded in the Case Report Form.

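### The primary non-inferiority comparison is a crude rate difference; stratifying by single versus multiple tumours would gain a little precision at almost no cost

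*Protocol article*

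**What the plan says.** Under Statistical methods for primary and secondary outcomes {20a}, the protocol article says that tumour organ, "single or multiple tumor tissues, and different ablation techniques were compared between the two groups to determine whether they were comparable". It gives no further use for these factors. The Statistical analysis method section attaches P values to the demographic and baseline comparisons.

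For the primary endpoint the same section states: "The overall response rate is compared using the chi-square test, corrected chi-square test, or exact probability test". It adds: "The 95% confidence interval of the difference in response rates between the two groups will be calculated". Non-inferiority is concluded if the lower limit lies above −10%. No stratum or covariate enters. The section on additional analyses {20b} repeats unadjusted tests for the secondary endpoints.

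Trial design {8} calls the trial a "multicenter, single-blind, randomized, parallel, positive-controlled clinical study". In the analysis, site is used only to list case numbers.

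Background and rationale {6a} cites a hepatocellular carcinoma study of intraoperative pain, "with a higher pain level in patients with multiple ablations than in those with one ablation" (6.76, SD 1.96, against 5.28, SD 2.48). It also says in general terms: "The degree and duration of pain vary according to interventional radiology technique". The data collection section {18a} lists among the surgical information "tumor type, number of tumors ablated, size and location of lesions, and ablation technique".

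**The concern.** The endpoint is a pain threshold, NRS at rest of 3 or less at every assessment. The article itself gives a reason to expect tumour number to predict pain, yet it uses that factor only in a comparability check. Under correct randomisation any baseline difference is due to chance, so a significance test of it answers no useful question, and the article attaches no action to the result. Three such tests at 0.05 would flag at least one difference in about 14% of correctly randomised trials if independent (1 − 0.95³ = 0.143).

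A prognostic factor known at baseline is better used in the estimate. The trial is planned at 80% power, so a small gain in precision that needs no extra patient is worth having. Fixing the adjustment in advance also removes the temptation to adjust afterwards because a baseline P value happened to be small.

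**Working it through.** **Inputs from the protocol article.** Effective rate 90% in both groups, margin 10 points, one-sided α 0.025, power 0.80, 1:1 allocation, 142 per group, 284 in total, about 316 after 10% dropout (Sample size {14}). Pain 6.76 (SD 1.96) against 5.28 (SD 2.48) for multiple against one ablation (Background {6a}).

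**Assumptions.** The documents give neither the share of patients with multiple tumours nor effective rates by stratum. The main range uses half the patients in each stratum, with rates of 95% single / 85% multiple and 98% / 82%. Both average 90%.

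**1. The plan's own figure.** n = (1.96 + 0.8416)² × (0.09 + 0.09) / 0.10² = 141.3, so 142 per group; 284 / 0.9 = 315.6, so 316. Both reproduce with the crude analysis.

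**2. Strength of the cited predictor.** Standardised difference = (6.76 − 5.28) / √[(1.96² + 2.48²)/2] = 1.48 / 2.235 = 0.66.

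**3. Variance after stratification, relative to crude.** The crude variance per patient is 0.9 × 0.1 = 0.09.
- 95% / 85%: (0.0475 + 0.1275)/2 = 0.0875; 0.0875/0.09 = 0.972, a fall of about 3%.
- 98% / 82%: (0.0196 + 0.1476)/2 = 0.0836; 0.0836/0.09 = 0.929, a fall of about 7%.

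**4. Half-width of the 95% interval at 158 per arm (316/2).**
- Crude: 1.96 × √(2 × 0.09/158) = 6.62 points.
- Stratified: 6.62 × √0.972 = 6.52 points; 6.62 × √0.929 = 6.38 points.
- Gain: 0.10 to 0.24 points.

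**5. Power at 142 per arm.** 100,000 simulated trials per scenario, with allocation not stratified by tumour number and true difference zero. The crude Wald interval is compared with a Mantel-Haenszel-weighted stratified difference.

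| Single / multiple rate | Share multiple | Crude | Stratified |
|---|---|---|---|
| 90% / 90% | 50% | 80.6% | 80.5% |
| 95% / 85% | 50% | 80.4% | 81.3% |
| 98% / 82% | 50% | 80.3% | 83.1% |
| 96% / 80% | 37.5% | 80.6% | 83.1% |
| 95% / 75% | 25% | 80.7% | 84.1% |

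At a true difference of −10 points the one-sided type I error was about 2.8% for both methods. The excess over 2.5% comes from the Wald approximation, not from the choice between crude and stratified.

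**The case against.** The strongest reply is that nothing here is invalid. A crude risk difference under randomisation is unbiased, the sample size was computed for it, and type I error is the same either way. All of that stands.

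A reader might infer that a chance imbalance in tumour number threatens the conclusion. At 158 per arm with half multiple, the 95% range of imbalance is 1.96 × √(2 × 0.25/158) = ±11 points. With gaps of 10 or 16 points between strata, that moves the crude difference by 1.1 or 1.8 points. But these are extremes of a variation that the crude interval already covers, so they cannot be counted again against the margin. The real gain is the narrowing in step 4.

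Other stronger readings also lack support:
- **Converting the cited scores to the trial endpoint.** A normal approximation puts 76% (one ablation) and 95% (multiple) at a score of 4 or more. That implies effective rates of 24% and 5%, which cannot be squared with the planned 90%. The cited scores are intraoperative pain in one tumour type, and they count ablations rather than tumours. They support a direction, not a size.
- **Organ, technique and centre as established predictors.** Technique has only a general statement; organ and centre have no figure, and the number of centres is not given.
- **Unstratified randomisation.** The article says only that computer-generated numbers and an interactive web response system are used. A condensed article may omit stratification or blocking.
- **All needed variables are in hand.** The article lists the number of tumours ablated as surgical information. The pump is connected 15 minutes before ablation, so the final count is known only after treatment starts. A recorded pre-treatment count is not confirmed.

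The baseline P values are poor practice but feed no decision rule. An unseen analysis plan might add supportive adjusted analyses. The article nevertheless fixes the crude comparison as primary, so the point does not rest on silence.

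**Conclusion.** The point holds as a modest improvement in efficiency, not as a defect of validity. The primary analysis leaves out a baseline factor that the article itself links to pain and already compares between groups. Under assumed rates from 95%/85% to 98%/82% in equal halves, stratifying cuts variance by about 3–7%, takes the half-width at 158 per arm from 6.6 to about 6.4–6.5 points, and adds about 1–3 points of power. The widest gap tried, 95%/75% with a quarter multiple, adds about 3.4. With no gap, power is unchanged apart from simulation error (80.6% against 80.5%). All these sizes rest on assumed stratum rates and shares. The planned sample size need not change.

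**What to change.** In the analysis plan, before unblinding, make the primary non-inferiority estimate a Mantel-Haenszel (or stratified Miettinen-Nurminen) risk difference with its 95% interval, stratified by single versus multiple tumours as known before randomisation. Only patients are blinded here, so the text should be settled before anyone compares outcomes by arm. Keep the −10% limit and report the crude difference as a sensitivity analysis.

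Confirm that the pre-treatment tumour count is recorded, and do not substitute the number actually ablated. Add centre only if randomisation was stratified by it, or if a rule for pooling small centres is set in advance. Describe baseline balance without P values.

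The cost is a few lines of analysis text and a check of the case report form. The main risk is sparse data: at 90% effective, about 32 failures are expected among 316 patients, so many strata would leave cells with few or none. That is why organ and technique, for which the article gives no figures, are left out of the strata.

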### Interim analyses {21b}

During the study, the study can be terminated early/the study center can be closed for the following reasons :(1) serious adverse events related to the experimental drug occur during the study; (2) the effect of the drug was found to be so poor that it was not necessary to continue the study; (3) it was found that there were significant errors in the clinical trial plan, and it was difficult to evaluate the drug effect; and (4) the pharmaceutical supervisory and administrative department or approved by the ethics commission has demanded an end to study early termination/close study center may be temporary, may also be permanent once decided to terminate research/close research center, the sponsor shall properly handle the relevant matters after the termination of research/close research center, and timely notify the research unit Good Clinical Practice. The archived research records shall be retained for future reference, and other relevant research materials (including partially completed blank research materials and investigatory drugs) shall be handed over to the sponsor according to the relevant requirements in the GCP.

### Methods for additional analyses (e.g., subgroup analyses) {20b}

Analysis of secondary efficacy indicators: the difference between the scores of NRS at each time point and the total score is compared by *t*-test or rank sum test; the difference between the physician satisfaction VAS score and the nurse satisfaction VAS score is compared by *t*-test or rank sum test; the difference between the rates of willing to undergo ablation surgery again is compared by chi-square test or corrected chi-square test or exact probability method; the difference between the duration of surgery is compared by *t*-test or rank sum test; the difference between the postoperative hospital stay is compared by *t*-test or rank sum test; the difference between the daily dosage is compared by *t*-test or rank sum test; the difference between the rates of uninterrupted completion of surgery without complaints of pain is compared by chi-square test or corrected chi-square test or exact probability method. Safety analysis: calculate the incidence of adverse reactions; systematically list the frequency and frequency of adverse reactions, and calculate the percentage; a detailed list of cases of various adverse events; a detailed list of cases of various adverse reactions; the number and rate of cases and conversion of physical examination indicators, ECG, respiratory and circulatory indicators, and laboratory indicators that “turn normal to abnormal” or “intensify abnormal” after the test; and list physical examination indicators, ECG, respiratory and circulatory indicators, and abnormal cases of laboratory indicators and clinical explanations.

### Methods in analysis to handle protocol non-adherence and any statistical methods to handle missing data {20c}

Not applicable. Non-compliance with the protocol and missing data, we plan not to use as part of the statistical analysis.

### Plans to give access to the full protocol, participant-level data and statistical code {31c}

The data shall not be used without the permission of the principal investigator in the responsible unit.

The principal investigator of the research unit will have full access to the final data so that the results can be properly analyzed and reported academically.

## Oversight and monitoring

### Composition of the coordinating center and trial steering committee {5d}

The group authorized a GCP-qualified clinical inspector to conduct surveillance.

### Composition of the data monitoring committee, its role, and reporting structure {21a}

The clinical study is subject to a quality assurance audit by the sponsor or a person authorized by the sponsor. GCP reviews may also be conducted by the drug approval department. Quality auditors and inspectors have access to all medical records, study-related documents and correspondence, and informed consent documents for the clinical trial.

### Adverse event reporting and harms {22}

#### Primary safety indicators

Incidence of common adverse reactions to opioid drugs, such as nausea, vomiting, vertigo, constipation, itching, urinary retention, hypoxemia, respiratory depression, drowsiness, delirium, and myoclonus are recorded. AEs are graded 1–5 according to the Common Terminology Criteria for Adverse Events 5.0 (CTCAE 5.0) of the National Cancer Institute (NCI).Grade 1: mild: asymptomatic or mild, clinical or diagnostic findings, no treatment required;Grade 2: moderate: minimal, local, or non-invasive treatment required, limiting age-appropriate instrumental activities of daily living;Grade 3: serious or medically significant but not immediately life-threatening, hospitalization or prolongation of hospitalization indicated, disabling, limiting self-care activities of daily living;Grade 4: life-threatening, urgent treatment required; andGrade 5: death related to AE.

If an AE is not listed in the NCI toxicity grading scale, it can be judged according to the following criteria:Grade I (mild): uncomfortable feeling, but does not affect normal daily activities;Grade II (moderate): uncomfortable degree enough to reduce or affect normal daily activities;Grade III (severe): unable to work or do normal daily activities; andGrade IV (fatal): disabling or fatal.

#### Secondary safety indicators

Physical examination: body temperature, respiration, pulse, heart rate, and blood pressure will be routinely measured; ECG and respiratory and circulatory parameters will be monitored during treatment;

Laboratory tests: hematology, biochemistry, and urinalysis.

#### Safety evaluation

##### Observation of AEs

Hypotension (0/1/2): Grade 0: systolic blood pressure (SBP) > 70% or 80/50 mm Hg before surgery; Grade 1: SBP < 70% or 80/50 mm Hg before surgery; Grade 2: SBP < 60% or 70/40 mm Hg before surgery. The patients who develop hypotension are treated with ephedrine.

Heart rate and heart rhythm changes (0/1): 1: heart rate less than 50 beats/min, more than 120 beats/min, or occurrence of arrhythmia; 0: otherwise. Atropine was given for the above conditions.

Hypoxemia (1/2/3/4): Grade 0: 96–100%; Grade 1: 91–95%; Grade 2: 86–90%; Grade 3: < 85%. If Hypoxemia occurred, jaw support was given, and if pulse oxygen saturation was < 90%, oxygen inhalation through a respiratory sac mask was provided.

Upper airway obstruction (0/1/2): Grade 0: no upper airway obstruction; Grade 1: mild snoring but normal oxygen saturation (SpO_2_) maintained; Grade 2: snoring, which must be relieved by oropharyngeal airway or jaw support, or normal SpO_2_ could not be maintained.

Respiratory depression/apnoea (0/1/2): Grade 0: respiratory rate > 12 times/min; Grade 1: 6 times/min < respiratory rate < 12 times/min; Grade 2: respiratory rate < 6 times/min.

Body movement (including retching and swallowing, limb movement) (0/1/2): 0: no body movement; 1: general body movement (toe movement, manual, not affecting the body movement examined); 2: severe body movement (leg movement or hip movement, affecting the body movement examined).

In the Case Report Form, the “Adverse Event Record Form” is maintained, and the investigators record in detail any AEs that occur in the case, particularly those related to analgesic medication. These must be recorded in the original data with medical terms and copied to the Case Report Form. The records of AEs shall include a description of AEs and all related symptoms, occurrence time, severity, duration, measures taken, final result, and outcome.

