### Sample size {14}

The sample size and case allocation included patients who underwent tumor ablation. NRS score (at rest) ≤ 3 points during operation and within 48 h after the operation was defined as effective. Assuming that the effective rate was 90% in the nalbuphine group and 90% in the morphine group, the clinical cut-off value for non-inferiority between the two groups was 10% if the nalbuphine group is non-inferior to the morphine group, setting one-sided α-error level = 0.025, *β* = 0.2 (power = 0.8), and the sample size ratio of the two groups 1:1. Overall, 142 patients were required for each group calculated using the PASS15.0 software, and a total of 284 patients were required for the two groups. Based on the dropout rate of 10% (284 ÷ 0.9 = 316), a total of approximately 316 patients were planned to be included.

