### Plans for communicating important protocol amendments to relevant parties (e.g. trial participants, ethical committees) {25}

Prior to the study inception, the study protocol was submitted to and approved by the Ethics Committee (approved on July 8, 2021). We are in the process of conducting this study. The first case enrollment was on October 11, 2021. All protocol modifications were determined after the final version of the study protocol was approved in writing by the Ethics Committee.

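### The safety section prescribes atropine for a heart rate above 120 and for any arrhythmia as well as for a rate below 50; for a fast rate the drug acts in the wrong direction

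*Protocol article*

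**What the plan says.** The relevant text is in the protocol article, section Adverse event reporting and harms {22}, under Safety evaluation, Observation of AEs. The item on heart rate and rhythm is scored 0 or 1. Code 1 is given for "heart rate less than 50 beats/min, more than 120 beats/min, or occurrence of arrhythmia; 0: otherwise". The management sentence follows at once: "Atropine was given for the above conditions".

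The item just before it concerns low blood pressure and has its own drug: "The patients who develop hypotension are treated with ephedrine".

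The same section requires each adverse event record to include "occurrence time, severity, duration, measures taken, final result, and outcome". Under Secondary safety indicators, "body temperature, respiration, pulse, heart rate, and blood pressure will be routinely measured", and the ECG is monitored during treatment.

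**The concern.** A rate below 50 and a rate above 120 are opposite deviations, and the printed text answers both with the same drug. A drug that moves heart rate one way cannot correct both. Since atropine speeds the heart, the fast rate is the one for which the rule is wrong. Arrhythmia without further description is also too broad a class for one drug.

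What is at stake is patient safety, not inference. The patients are receiving an opioid by pump around an ablation procedure, under monitoring that will detect these events. Followed literally, the rule gives a patient whose heart rate exceeds 120 a drug that raises it further.

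A lesser point is that the 0/1 code alone does not tell the three events apart. This affects how the results read in a table. It is not a loss of data.

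**Working it through.** No figure in the plan needs to be reproduced, so the check is a reading of the text with a little counting.

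**1. What does the atropine sentence refer to?** It uses the plural and directly follows the list of three conditions in the heart-rate item. It cannot sensibly refer to hypotension, which has a separate paragraph and a separate drug, ephedrine.

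**2. Does any other text narrow it?** Atropine appears nowhere else in the article. The sections that might have limited the rule do not:

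- *Relevant concomitant care {11d}* bars newly added analgesics and allows drugs that leave opioid efficacy unaffected. It says nothing about heart-rate treatment.
- *Provisions for post-trial care {30}* and *Plans to promote participant retention {18b}* contain general statements that harms will be treated and that the investigator decides on treatment. Neither mentions heart rate.
- *Secondary safety indicators* says what is measured, not how it is treated.

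**3. Does the drug fit each condition?** The one outside premise is that atropine raises heart rate.

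| Condition coded 1 | Drug assigned | Fit |
|---|---|---|
| Rate below 50/min | Atropine | Suitable direction |
| Rate above 120/min | Atropine | Opposite direction |
| Any arrhythmia | Atropine | Depends on type |

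Atropine is assigned to 3 of 3 conditions. It fits 1, is opposite in direction for 1, and is undetermined for 1.

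**4. Contrast within the same section.** The hypotension item pairs one drug with a deviation in one direction. The heart-rate item pairs one drug with deviations in both directions.

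**5. Scale.** The article gives no rate for any of the three events, and none is assumed here. According to Sample size {14}, "a total of approximately 316 patients were planned to be included". Each 1% of patients with a rate above 120 would be 0.01 × 316 = 3.16, or about 3 patients.

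**6. Timing.** "The first case enrollment was on October 11, 2021", and the article was published on 22 October 2022. That is 365 + 11 = 376 days, about 12 months, during which the rule may have been in force. It measures elapsed time only; it does not show that any patient was treated this way.

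**7. Can the three events be separated afterwards?** Yes. Heart rate and ECG are observed, and the adverse event record describes each event and the measures taken.

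**The case against.** The strongest reply is that this is a slip of wording and not a decision. The sentence sits in a list of grading codes with brief remarks on management, is in the past tense, and has loosely edited neighbours: the hypoxemia item is labelled 1 to 4 but its grades run from 0 to 3. Nothing suggests that anyone chose atropine for tachycardia. Treating staff are not blinded, they work under ECG monitoring, and the article elsewhere leaves the treatment of harms to the investigator, so few clinicians would apply the sentence mechanically. The full protocol (V1.2) may word it correctly. No tachycardia event or misuse of atropine is reported, and no statistical quantity depends on the sentence.

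Most of this stands, and it lowers the likelihood of harm. A slip is the likeliest explanation, and the case for actual harm is unproven. But the reply does not repair the text. This is a specific instruction that is printed wrongly, not a detail left out when the article was condensed. The past tense is no defence, because the hypoxemia remedy in the same section is also written in the past tense and plainly describes management. A safety rule in a multicenter trial should not depend on sites disregarding it.

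The objection also holds that separate table rows for the three events are a matter of layout that an analysis plan would normally settle. The article already plans a detailed listing of adverse event cases and of ECG and circulatory changes. That part is a preference and is treated as optional below.

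**Conclusion.** The concern holds for the text as printed. The rule assigns atropine to three conditions; it suits one, works in the wrong direction for one, and depends on type for one. This rests on the plain reading of the sentence and on one undisputed pharmacological fact, that atropine raises heart rate.

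It is not established that the sites follow this rule or that any patient was affected, and the full protocol may limit the sentence. The number of patients at risk cannot be stated from the article beyond about 3 for each 1% of those planned. Sample size, error rates, the non-inferiority comparison and the analysis sets are unaffected. The point should be corrected because it concerns a safety instruction in a recruiting trial, but it does not threaten the trial's validity.

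**What to change.** Replace the sentence with: *Atropine is given for a heart rate below 50 beats/min. A heart rate above 120 beats/min or an arrhythmia is managed according to its type, as confirmed by the clinical investigators.*

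Check how the full protocol words this, and tell the sites if it carries the same error. For patients already coded 1, look at the recorded measures taken, to see whether anyone with a fast rate or an unsuitable arrhythmia received atropine.

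Optionally, show low rate, high rate and arrhythmia as three lines by arm in the safety tables.

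The cost is a two-sentence clarification and a short review of existing adverse event records. No new data are needed, because heart rate, ECG and measures taken are already collected.
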